### Screening and eligibility assessment

For potential participants with a diagnosis of NAFLD, screening will be undertaken by the clinical care team through direct confirmation of age, establishing that there is a diagnosis of NAFLD and that they either have a liver biopsy scheduled or have had a liver biopsy within the last 12 months. Potential participants will be provided with a letter of invitation and a patient information leaflet (PIL) either at the time of their routine NHS clinic visit or sent by post. For potential control participants without NAFLD, screening of the existing OBB database will be undertaken and a letter of invitation and PIL will be sent by members of the OBB research team.

Specific inclusion and exclusion criteria are detailed below. There will be no exceptions made regarding eligibility and each participant must satisfy all the approved inclusion and exclusion criteria of the protocol.

### Inclusion criteria

#### Participants with NAFLD

Participant is willing and able to give informed consent for participation in the study.Patients with a diagnosis of NAFLD who are scheduled for a liver biopsy, or the patient has had a liver biopsy with a confirmed diagnosis of NAFLD within the last 12 months.Aged ≥18 years.

#### Control participants without evidence of NAFLD

Participant is willing and able to give informed consent for participation in the study.Bottom 25th percentile of HOMA-IR in OBB.BMI <35 kg/m^2^.Fasting triglycerides <2.0 mmol/L.Aged ≥18 years.

### Exclusion criteria

#### All participants

Insufficient understanding of written and verbal English.The participant has not had sufficient time to read the PIL and understand the study requirements.Hepatic steatosis, inflammation or fibrosis with a primary aetiology other than NAFLD.

### Study procedures

All participants will personally sign and date the latest approved version of the informed consent form before any study-specific procedures are performed. Written and verbal versions of the PIL and informed consent forms will be presented to the participants detailing the exact nature of the study, what it will involve for the participant, the implications and constraints of the protocol and any risks involved in taking part. It will be clearly stated that the participant is free to withdraw from the study at any time for any reason without prejudice to their future care, without affecting their legal rights and with no obligation to give the reason for withdrawal. The participant will be allowed as much time as possible (and this may be less than 24 hours) to consider the information, and the opportunity to question the investigators, their general practitioner or other independent parties to decide whether they will participate in the study. Consent may be obtained, and the study procedures performed on the same day. The person who obtains the informed consent will be suitably qualified, experienced and have been authorised to do so by the chief/principal investigator. A copy of the signed informed consent form will be given to the participant. The original signed form will be retained at the study site. The study is not randomised. Participants will be enrolled as they are consented. At enrolment, all participants will be assigned a unique identification number in a sequential order.

For all participants, demographic data will be collected including age, sex, ethnicity, height, weight and calculated BMI. Details of the participants’ clinical history will also be collected, including any relevant medical history (smoking, type 2 diabetes, hypertension, cardiovascular disease and alcohol use) as well as details of concomitant prescribed medications. Patients with NAFLD will usually have routine blood tests as part of their clinical care consultation and therefore the additional blood samples that will be collected will not require additional venepuncture (although this may be needed if a participant attends for a dedicated research visit that is separate from their clinical care appointment). A dedicated research visit is required for all participants without NAFLD that will include collecting demographic data and clinical history as well as venepuncture and providing a 10 mL urine sample. Vibration-controlled transient elastography (VCTE) is frequently used in hepatology clinics to determine the risk of advanced fibrosis and can provide both a measure of liver stiffness (indicative of fibrosis stage) and a controlled attenuation parameter that correlates with the degree of hepatic steatosis.^18 19^ Where available, these data will be recorded for all patients with NAFLD.

All blood sample analyses will include measurement of a full blood count, renal function and electrolytes, liver chemistry (including alanine aminotransaminase (ALT), aspartate aminotransaminase (AST), alkaline phosphatase, gamma-glutamyltransferase, bilirubin, albumin, ferritin), total and high-density lipoprotein-cholesterol and triglycerides as well as glycated haemoglobin. In addition, samples will be analysed for the ELF panel^20^ (hyaluronic acid, type III procollagen peptide and tissue inhibitor of matrix metalloproteinase 1). Calculations for non-invasive risk score to detect advanced fibrosis will also be made including NAFLD Fibrosis Score (NFS), Fib-4, AST to Platelet Ratio Index (APRI), Fibroscan-AST (FAST) and BMI, AST/ALT Ratio, Diabetes Mellitus (BARD) .^21–25^

Liver biopsy data will be collected to include the NAFLD Activity Score grading with its individual components of steatosis, lobular inflammation, and ballooning and also the fibrosis staging (graded F0–F4) according to the Kleiner classification.^26^

A 10 mL urine sample will be collected from all participants, aliquoted and stored at −80°C until analysis. Predefined steroid hormone metabolites will be measured using gas chromatography-mass spectrometry and liquid chromatography-tandem mass spectrometry (LC-MS-MS) as described previously.^27 28^ The steroid metabolite data will then be subjected to machine learning employing a GMLVQ^17^ classifier that was trained on retrospective data. Its performance to identify participants with advanced fibrotic NAFLD compared against other non-invasive biomarker strategies (Fib-4, NFS, BARD, APRI, AST/ALT, ELF, FAST, VCTE) will be evaluated.

### Statistical methods, sample size and analysis plan

The study has been planned and designed with expert statistical advice and an experienced statistician is part of the investigative team.

### Sample size

We will aim to recruit at least 460 participants to the TrUSt-NAFLD study (NAFLD n=310; control n=150). Sample size and power calculations have been based on our previous published data.^17^ Our primary analysis will aim to distinguish patients with mild (F0–F2) versus advanced fibrosis (F3–F4). Through the recruitment of 310 participants with NAFLD, we will have 85% power to identify a difference in sensitivity between technologies of 12 percentage points (80% vs 92%) assuming a 5% significance level, a prevalence of 50% (ie, 50% of the participants will be F0–F2 and 50% F3–F4) and independence of comparative test results. The estimates of sensitivity and the difference in sensitivity have been estimated from previous work.^14^

### Analysis of outcome measures

Data for all participants who complete the study will be included in the analysis. If any participants withdraw from the study, samples and data collected will not routinely be destroyed and will be used in the analysis unless requested not to do so by the individual. Statistical analysis will be undertaken at the end of study and after the analysis of all the samples has been completed.

The primary outcome of the TrUSt-NAFLD study is to determine the accuracy of the urine steroid metabolome GMLVQ algorithm to distinguish early (F0-2) from advanced (F3–F4) NAFLD fibrosis. Sensitivity, specificity and negative and positive predictive values will be calculated with 95% CIs. Additionally, ROC curves will be generated and the AUC will be calculated.

Secondary and exploratory outcomes will include a comparison of the performance of the urine steroid metabolome GMLVQ algorithm against other non-invasive NAFLD biomarkers (Fib-4, NFS, BARD, APRI, AST/ALT, ELF, FAST, VCTE). Data from participants with NAFLD will also be compared against control participants without evidence of NAFLD to determine the ability of the algorithm to detect NAFLD (across the spectrum of its severity) in the general population. Finally, exploratory analyses detecting steroid metabolites using LC-MS-MS in serum samples and subsequently incorporating the GMLVQ algorithm will be performed and compared against the urine analysis.

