**Trial registration number:**

ISRCTN19370855.

STRENGTHS AND LIMITATIONS OF THIS STUDYThe participants recruited with non-alcoholic fatty liver disease will all have had a liver biopsy to stage their disease severity as well as multiple other non-invasive biomarkers that are currently used in clinical practice.The study includes a well-matched and phenotyped control cohort without evidence of liver disease, prospectively recruited from an existing biobank.A urinary test has high patient acceptability and is less operator dependent than other non-invasive tests such as transient elastography.The study is cross-sectional and not longitudinal, so will not be able to address questions as to the utility of biomarker strategies and disease progression/remission.The study will recruit patients having a liver biopsy as part of routine clinical care which may introduce a degree of selection bias, creating a cohort more likely to have advanced (as opposed to mild) disease severity.

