The liver is the main site of steroid metabolism and there is disruption of specific pathways in patients with NAFLD,^15 16^ providing biological plausibility to our approach. The pilot study showed an increased activity in 11β-hydroxysteroid dehydrogenase type 1 and 5α reductase in patients with advanced fibrosis.^17^ Steroid 5β reductase (AKR1D1), which is mostly expressed in the liver, has also been shown to decrease as fibrosis in NAFLD progresses.^16^ When coupled with machine learning-based analysis using, for instance, Generalized Matrix Learning Vector Quantization (GMLVQ), a global assessment of hepatic steroid hormone metabolism can be made. GMLVQ is a supervised machine learning technique whereby an algorithm is trained using known datasets, and then subsequently applied to unknown samples. GMLVQ is able to simplify complex data into clusters of patients who have a high risk of having advanced fibrotic NAFLD. Data from our published proof-of-principle study indicate that this is tightly influenced by NAFLD stage.^17^ As part of this discovery study, we analysed urine samples from 227 subjects (121 with biopsy-proven NAFLD and 106 controls). GMLVQ analysis achieved excellent separation of early (F0–F2) from advanced (F3–F4) fibrosis (area under the curve-receiver operating characteristic curve (AUC-ROC): 0.92 (0.91–0.94)). There was near perfect separation of healthy controls from patients with advanced fibrotic NAFLD and from those with NAFLD cirrhosis. Further refinement of the model incorporated the 10 most discriminatory steroids as well as patient age and body mass index (BMI) which has further enhanced diagnostic performance.^17^

The aim of the current study is to prospectively validate our published findings in an independent cohort of patients undergoing routine liver biopsy for NAFLD and to compare the performance of the machine learning-based urine steroid metabolome test against other non-invasive biomarker strategies that are currently used in clinical practice.

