### Setting and participants

The study will take place in secondary care hospital settings in eight dedicated hepatology clinics across the UK. Patients (male or female) aged ≥18 years, who are attending or have attended an NHS clinic for the diagnosis and/or management of NAFLD and who are scheduled to have a liver biopsy or who have had a liver biopsy to stage NAFLD within the last 12 months will be approached to participate. Control participants without evidence of NAFLD will be recruited from the OBB based at the Oxford Centre for Endocrinology, Diabetes and Metabolism, Churchill Hospital, Oxford, UK.

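### Recruiting only patients biopsied in routine care distorts the head-to-head comparison unequally for any marker that helped decide the biopsy (VCTE at least), and the article discloses only a general shift in severity

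*Protocol article*

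**What the plan says.** Under Setting and participants, the NAFLD cohort is limited to patients "scheduled to have a liver biopsy or who have had a liver biopsy to stage NAFLD within the last 12 months". Biopsy is a decision of the treating clinic, not a study procedure.

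The Introduction sets a two-part aim: validate the urine test in patients having routine biopsy, and compare it "against other non-invasive biomarker strategies that are currently used in clinical practice". Analysis of outcome measures lists the second part as a secondary or exploratory "comparison of the performance of the urine steroid metabolome GMLVQ algorithm against other non-invasive NAFLD biomarkers (Fib-4, NFS, BARD, APRI, AST/ALT, ELF, FAST, VCTE".

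Study procedures says that VCTE "is frequently used in hepatology clinics to determine the risk of advanced fibrosis", and adds: "Where available, these data will be recorded for all patients with NAFLD".

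The strengths-and-limitations list concedes: "The study will recruit patients having a liver biopsy as part of routine clinical care which may introduce a degree of selection bias". It describes the consequence as "creating a cohort more likely to have advanced (as opposed to mild) disease severity". It does not say that the selection may act differently on the tests being compared.

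**The concern.** A shift in disease severity does not by itself favour one test over another. Selection on one test's own result does. If a raised VCTE reading makes biopsy more likely, the biopsied cohort holds too few patients with low readings. Within it VCTE has a restricted range, so it discriminates less well. More of the F0–F2 patients are VCTE-positive, so specificity falls. Fewer of the F3–F4 patients are VCTE-negative, so sensitivity rises. The urine result was unknown when the biopsy was decided, so it is affected only through its correlation with the marker.

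Two equally accurate tests would then look different. The urine test would look better on AUC and specificity and worse on sensitivity, which is the measure in the Sample size section. The comparison is half of the stated aim, and the Discussion looks to changing how NAFLD is diagnosed and staged. A reader may therefore carry the contrast to patients before the biopsy decision, where it does not hold.

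**Working it through.** **The plan's own figure.** Sample size gives 85% power for 80% vs 92% sensitivity, with 310 patients, half of them F3–F4 (155), 5% significance and independent test results. I assume a two-sided test.
- Pooled two-proportion: (0.12·√155 − 1.96·√(2·0.86·0.14)) / √(0.8·0.2 + 0.92·0.08) = 1.10, so power is 86.5%.
- Paired (McNemar), discordance 0.92·0.2 + 0.8·0.08 = 0.248: (0.12·√155 − 1.96·√0.248) / √(0.248 − 0.12²) = 1.07, so power is 85.8%.

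The stated 85% is reproduced. The question is what selection does to the quantities compared.

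**Assumed inputs (none is in the documents).** Equal-variance binormal scores; true AUC 0.80 for both tests, so the class means differ by √2·Φ⁻¹(0.80) = 1.190; clinic prevalence of F3–F4 35%; marker cut-off at 80% clinic specificity, giving 63.6% sensitivity. Biopsy occurs with probability a above the marker's clinic median and b below it. Of F3–F4 patients 78.6% lie above that median, and of F0–F2 patients 34.6%.

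**Sensitivity and specificity among the biopsied.** The cut-off lies above the median, so
- sensitivity = a·0.636 / (a·0.786 + b·0.214)
- specificity = 1 − a·0.200 / (a·0.346 + b·0.654)

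| Selection (a vs b) | Prevalence among biopsied | Marker sensitivity | Marker specificity |
|---|---|---|---|
| none | 35% | 64% | 80% |
| 65% vs 35% | 41% | 71% | 71% |
| 80% vs 20% | 47% | 76% | 61% |
| 100% vs 0% | 55% | 81% | 42% |

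The marker's sensitivity rises by 7 to 17 points. The two stronger scenarios bracket the 50% prevalence that Sample size assumes.

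**AUC gap (urine minus marker; true gap zero).** Simulation with 2,000,000 patients per correlation:

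| Selection | Within-class correlation 0 | 0.3 | 0.5 |
|---|---|---|---|
| 65% vs 35% | 0.013 | 0.007 | 0.005 |
| 80% vs 20% | 0.040 | 0.024 | 0.015 |
| 100% vs 0% | 0.098 | 0.060 | 0.038 |

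In the last row the marker's AUC is 0.70. The urine AUC stays at 0.80 under independence but falls to 0.76 at correlation 0.3.

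**Chance of a spurious urine advantage.** Hanley–McNeil standard errors with 155 and 155 patients are about 0.030 (AUC 0.70) and 0.025 (AUC 0.80), so the difference has a standard error of about 0.039 if the tests are independent. The chance is 1 − Φ(1.96 − gap/0.039): 18% for a gap of 0.04 and 73% for 0.10, against 2.5% without distortion.

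**Link to the 12-point target.** Let r be the ratio of biopsy probabilities, marker-positive to marker-negative. A true sensitivity of 80% is observed as 0.8r/(0.8r + 0.2): 85.7% at r = 1.5, 88.9% at r = 2 and 92.3% at r = 3. If the urine test stays at 92%, power falls from about 86% to 42% at r = 1.5 and 15% at r = 2; at r = 3 the gap has gone.

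**Does conditioning help?** With equal correlation 0.3 between tests, the log-odds coefficient of the urine score is 1.190/1.3 = 0.92 given one marker and 1.190/1.6 = 0.74 given two. If the model contains the marker that drove referral, the coefficient in the biopsied matches that in all patients. If it contains only some other marker, 0.92 becomes 0.82 under hard selection and about 0.87 to 0.88 under 80% vs 20%. With both markers entered jointly it stays at 0.74 to 0.75 in all patients and in the biopsied.

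**The case against.** The strongest reply is that the Introduction already names patients having routine biopsy as the population. For asking which test might spare a biopsy among those now sent for one, a marker's accuracy after clinic triage is its real accuracy there. That stands: the contrast is a valid description of that group. It misleads only when carried further.

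A reader might infer that all eight comparators decide who is biopsied. The documents do not support this. The statement is close to explicit for VCTE only, and VCTE is recorded where available. Being in clinical use does not mean that a marker triggers biopsy. Study procedures describes ELF as run on study samples and the scores as calculated for the study, and sampling may fall up to 12 months from biopsy. The analysed value need not be the one the clinic saw. A comparator that played no part in referral is affected only indirectly, as the urine test is.

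A reader might also infer that the comparison is tilted towards the urine test and will often yield false superiority. The direction is mixed: on sensitivity the distortion works against the urine test. The high false-positive chance needs hard selection and independence together. Some correlation is likely, since the refined urine model includes age and BMI and BMI also enters BARD. If the 80% sensitivity behind the sample size came from biopsied cohorts, it already carries part of the effect. That source is not shown, so the power losses are illustrative.

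Finally, the comparison is secondary or exploratory, and the article does disclose selection in general terms. Both are true. They limit the weight of the point without answering the unequal effect.

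**Conclusion.** The point holds for any marker that influenced referral: VCTE on the document's own description, others plausibly. Relative to the clinic population before the biopsy decision, such a marker's AUC and specificity are understated in this cohort and its sensitivity at a fixed cut-off is overstated, while the urine test is less affected. No passage recognises this.

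The size cannot be derived from the documents. Under the stated assumptions (AUC 0.80 for both tests, 35% clinic prevalence, selection on one marker) the spurious AUC gap is about 0.005 with mild selection and correlation 0.5, and 0.10 with hard selection and independence. The marker's sensitivity rises by about 7 to 17 points; the upper end exceeds the 12-point difference in Sample size.

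The evidence does not show that the head-to-head is invalid or should be replaced. It justifies a supplementary analysis and a limit on interpretation: a cheap improvement, not a flaw in the primary outcome.

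**What to change.** Keep the comparison in Analysis of outcome measures and add three things.

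1. An added-value analysis: a logistic model for F3–F4 with the referral-relevant markers entered jointly as continuous values (VCTE where available, plus serum markers that the clinic had before biopsy), reporting what the urine score adds. One model per comparator is not enough, because it leaves bias when a different marker drove referral.
2. One case-report item, taken from existing clinic notes, recording which non-invasive results informed the biopsy decision. Repeat the head-to-head for markers, or in patients, where the marker did not drive referral.
3. A statement that unadjusted AUC, sensitivity and specificity contrasts apply to biopsy-referred patients and will not be used alone to claim superiority over a marker that drove referral. The limitations list should mention the unequal effect.

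The cost is a little more analysis, an item that will be missing for some patients, a smaller sample where VCTE is unavailable, and a narrower superiority claim. No new patients, samples or visits are needed.

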### Recruitment

The TrUSt-NAFLD study will recruit patients with a diagnosis of NAFLD from dedicated NHS hepatology clinics. The initial approach for participants to be part of the study will be made by members of the team directly involved in their clinical care. In some situations, an alternative recruitment strategy whereby patients (who have consented to be approached for future research) are contacted having been identified from existing clinical databases may be employed. To ensure sufficient recruitment of patients, eight centres across the UK will participate in the study. Interested potential participants will be seen during their routine NHS clinic visit by the research team to confirm eligibility. Those patients identified from existing databases will be contacted by letter and their eligibility will have been assessed prior to contact by lead clinicians and researchers within the dedicated hepatology team.

Recruitment of control participants without NAFLD will use the OBB; a biobank of >9000 volunteers in Oxfordshire, UK, who have undergone extensive metabolic phenotyping and consented to be reapproached for clinical research. In order to try to ensure the absence of significant liver disease, individuals with a Homeostatic Model Assessment for Insulin Resistance (HOMA-IR) (as a marker of global insulin resistance) (https://www.dtu.ox.ac.uk/homacalculator/) in the lowest 25%, BMI <35 kg/m^2^ and fasting triglyceride levels <2 mmol/L will be invited to participate. HOMA-IR, triglycerides and BMI are all measured and recorded as part of the detailed OBB metabolic phenotyping and therefore can be used in a recall-by-phenotype strategy. Invitations to take part in the study will be sent with an aim of recruiting 60% male and 40% female participants to match the anticipated sex distribution in the NAFLD cohort which has been estimated from local liver biopsy data. Only individuals with normal liver biochemistry and non-invasive serum markers (including the enhanced liver fibrosis (ELF) panel) indicating low risk of advanced NAFLD will be included in the study.

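### Comparing biopsied clinic patients with volunteers selected for low metabolic risk cannot show how well the algorithm detects NAFLD in the general population, and calling those controls well matched conflicts with how they are chosen

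*Protocol article*

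**What the plan says.** Under Analysis of outcome measures, among the secondary and exploratory outcomes, the article states: "Data from participants with NAFLD will also be compared against control participants without evidence of NAFLD", and gives the purpose as "to determine the ability of the algorithm to detect NAFLD (across the spectrum of its severity) in the general population".

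**Cases.** Setting and participants says: "The study will take place in secondary care hospital settings in eight dedicated hepatology clinics across the UK". Patients must have a biopsy scheduled or have had one within the last 12 months. The strengths and limitations list accepts that recruiting from routine biopsy may introduce selection bias, "creating a cohort more likely to have advanced (as opposed to mild) disease severity".

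**Controls.** The inclusion criteria require "Bottom 25th percentile of HOMA-IR in OBB", BMI below 35 kg/m² and fasting triglycerides below 2.0 mmol/L. Recruitment adds a further filter: "Only individuals with normal liver biochemistry and non-invasive serum markers (including the enhanced liver fibrosis (ELF) panel) indicating low risk of advanced NAFLD" may enter.

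**Matching.** The strengths and limitations list says: "The study includes a well-matched and phenotyped control cohort without evidence of liver disease". The abstract also calls the controls appropriately matched. The only matching described is in Recruitment: invitations aim for 60% men and 40% women, to mirror the sex mix expected in the NAFLD cohort.

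**The concern.** The aim names a target population that neither arm represents. A test used in the general population must give a negative result in people who are insulin resistant or have raised triglycerides but do not have NAFLD, and a positive result in people with mild, undiagnosed NAFLD. The control criteria exclude the first group. Recruiting cases through biopsy clinics under-represents the second. What remains is a comparison of the two ends of the spectrum.

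Carrying out the study perfectly would not cure this, because the limitation lies in who is sampled. A good AUC from this contrast could be reported as evidence of population-level detection that the study does not contain. The Discussion anticipates a change in how NAFLD is both diagnosed and staged. Within this study, the contrast with controls is the only one that bears on NAFLD versus no NAFLD.

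The matching labels add to the problem. Selecting controls, and only controls, on low insulin resistance makes the groups less alike on a feature closely tied to the disease. A reader who takes the strengths list at face value would assume the opposite.

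**Working it through.** **1. The plan's own figure.** The Sample size section states 85% power for sensitivity 80% versus 92%, with 310 NAFLD participants, half of them F3–F4 (155), a 5% level and independent test results. Using McNemar's test under independence:
- Discordant proportions: 0.92 × 0.20 = 0.184 and 0.80 × 0.08 = 0.064. Their sum is 0.248 and their difference 0.12.
- Power = Φ[(0.12·√155 − 1.96·√0.248) / √(0.248 − 0.12²)] = Φ(1.07) = 85.8%.

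The pooled two-proportion formula gives 86.5%. The stated figure reproduces and is not at issue. It concerns the fibrosis-stage comparison; no size or power figure is given for the comparison with controls.

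**2. Target population against sampled groups.**

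| | General population, from the article | Sampled |
|---|---|---|
| Share with NAFLD | About one in four (Abstract); up to 30% (Introduction) | 310/460 = 67.4%, fixed by design |
| Severity of NAFLD | Whole spectrum | Biopsied clinic patients, acknowledged to favour advanced disease |
| People without NAFLD | All levels of insulin resistance and triglycerides | Lowest HOMA-IR quarter, triglycerides below 2 mmol/L, normal liver tests, low-risk ELF |

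The HOMA-IR rule alone makes about three quarters of the source biobank ineligible. The Introduction puts NAFLD at up to 60% in patients with diabetes and obesity, so at least 40% of that group do not have it. These are people a population test must classify correctly, and the control rules largely remove them.

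**3. Possible optimism (illustration; all inputs assumed).** Suppose that, among people without NAFLD, the classifier score and HOMA-IR (suitably transformed) are bivariate normal with correlation ρ. Set the true specificity at 0.80 and the true AUC at 0.80 against everyone without NAFLD, with case scores normal and of unit variance. Restricting controls to the lowest HOMA-IR quarter gives an apparent specificity of P(score < t | HOMA-IR in lowest quarter), where t is the 80th percentile of the unrestricted score. The AUC is computed in the same way.

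| ρ | Apparent specificity | Apparent AUC |
|---|---|---|
| 0 | 0.80 | 0.80 |
| 0.2 | 0.87 | 0.85 |
| 0.3 | 0.90 | 0.87 |
| 0.4 | 0.93 | 0.89 |
| 0.5 | 0.95 | 0.91 |

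This takes the quarter among people without NAFLD, whereas the criterion takes it in the whole biobank. If one in four biobank members had NAFLD and none of them fell in the lowest quarter, the eligible share of those without NAFLD would be 0.25/0.75 = 33%. The same integral at 33% gives a specificity of 0.86 to 0.94 and an AUC of 0.84 to 0.90 for ρ from 0.2 to 0.5. The pattern is the same. The triglyceride, biochemistry and ELF filters are not modelled.

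**4. Predictive values (relevant only if someone calculates them here).** PPV = Se·p / [Se·p + (1 − Sp)(1 − p)]. With assumed Se = 0.90 and Sp = 0.90, PPV is 94.9% at p = 67.4%, 75.0% at 25% and 79.4% at 30%. With Sp = 0.80 it is 90.3%, 60.0% and 65.9%.

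**The case against.** The strongest defence is that the control criteria have a stated reason and are fully disclosed. Controls cannot ethically be biopsied, so strict phenotype selection is the means of keeping unrecognised liver disease out. Looser criteria would put unverified NAFLD among the controls. The outcome is secondary or exploratory, and the primary analysis uses NAFLD participants only. All of this stands. It justifies the choice of controls, but not the population named in the aim, and neither the limitations list nor the Discussion names control selection as a limit.

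Several stronger readings are tempting, and the article does not support them:

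- **BMI is forced apart, or obese people are excluded.** Controls may have a BMI up to 35 and cases have no BMI floor. Selection on insulin resistance and triglycerides is imposed; a BMI gap is not.
- **The classifier will separate the groups on age and BMI alone.** The Introduction says a refined model "incorporated the 10 most discriminatory steroids as well as patient age and body mass index (BMI"). The Abstract and Study procedures, however, describe applying the classifier to steroid metabolite data. Which version is used here is not stated, so this concern is conditional. An AUC for BMI alone would need BMI means and SDs that the article does not give.
- **Age is unmatched.** The article describes only sex matching, but a condensed article may leave other variables to the full protocol.
- **Misleading predictive values or unfair head-to-heads are planned.** PPV and NPV are listed under the primary outcome, and Study procedures frames the marker comparison around advanced fibrosis. Neither is stated for the contrast with controls.

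**Conclusion.** The concern holds for the wording of the aim and for the matching labels. As designed, the comparison can show discrimination between biopsied NAFLD patients and selected metabolically low-risk volunteers. It cannot show detection in the general population. That conclusion follows from the entry criteria alone and needs no numerical assumption.

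The direction of error in specificity and AUC is likely to be optimistic, to the extent that the score tracks metabolic status. The size cannot be computed from the article. The illustrative rise from 0.80 to between 0.87 and 0.95 in specificity rests on assumed correlations of 0.2 to 0.5, normality and an assumed true value. At zero correlation the HOMA-IR rule adds no inflation, although the extrapolation would still be unsupported.

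A reader might infer that the study's main result is compromised. It is not: the F0–F2 versus F3–F4 analysis and its power calculation do not use the controls. This should be fixed, but it is not an obstacle to the primary objective.

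**What to change.** 1. Restate the aim as discrimination between biopsied NAFLD patients and selected metabolically low-risk volunteers, labelled exploratory, and drop the reference to the general population.
2. Replace the matching claims in the abstract and the strengths list with the attributes actually matched. On the article's own description that is the sex distribution, plus any others the full protocol specifies.
3. Add control selection to the limitations, beside the case-selection bias already listed.
4. Report the contrast adjusted for age, sex and BMI. If the version of the classifier that includes age and BMI is used, show beside it a benchmark AUC from age and BMI alone.
5. As a safeguard, derive no PPV or NPV from the 310:150 mix. Make no head-to-head with ELF or scores based on liver biochemistry in this contrast: those markers are entry filters for controls, so their specificity would be favoured by construction.

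The cost is a few wording changes and one adjusted analysis. Age, sex and BMI are already collected for all participants under Study procedures, and no extra recruitment is needed. The downside is a narrower secondary claim.
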